#### Adherence and per-protocol analyses

For the 12-week Treatment Phase, adherence is defined as follows: ≥75% attendance to recommended yoga classes (i.e., 9 or more); ≥73% attendance to PT sessions (i.e., 11 or more); self-reported completion of three-fourths or more of the assigned educational materials.

For the 40-week Maintenance Phase, adherence is defined as follows: ≥75% attendance to maintenance yoga classes for structured maintenance yoga participants and ≥4 (80%) maintenance PT sessions for structured maintenance PT participants. There is no formal adherence definition for the three other groups: no structured maintenance yoga, no structured maintenance PT, or education. However, for these groups, we collect self-report data on attendance to any non-study yoga/exercise/gym classes and home practice during the Maintenance Phase.

Per-protocol analyses will include those participants adherent to their assigned protocol. If a yoga participant starts PT, a PT participant practices yoga, or an education participant starts PT or yoga, that participant would also be excluded from the per-protocol analysis.

Additional sensitivity analyses will be performed to explore the potential role of concomitant interventions as follows:

•Analyze participants who were adherent with the protocol as defined above but also exclude any participants who received any operative procedures during the study (i.e., epidural steroid injection or back surgery).

•Analyze participants who were adherent with the protocol as defined above but excluding anyone who started new treatments for back pain (e.g., medication, chiropractic, acupuncture, massage).

•Create an ordinal variable for the number of different non-protocol treatments a participant uses during the study period and analyze participants who were adherent with the protocol as defined above while adjusting for this non-protocol treatment variable.

#### Cost effectiveness analyses

From the society perspective, a cost-utility analysis will be performed by comparing the incremental societal costs of one treatment arm over another (direct medical and non-medical costs plus productivity costs) to incremental effectiveness in terms of change in QALYs [52]. This is designated as the “reference case” and can be used by policy makers for the broad allocation of health resources [97,100]. For the third-party payer perspective, incremental costs will only include direct medical costs (direct intervention costs plus ongoing direct medical utilization costs) and will be compared to the incremental QALY impact. This analysis will help determine whether it makes economic sense for yoga to be a reimbursable service for this population. For the participant perspective, cost-effectiveness will be determined by comparing participants’ incremental out-of-pocket costs (travel, childcare, over-the-counter medications, use of non-reimbursed healthcare practitioners, co-payments, cost of yoga or PT sessions attended after the 12-week Treatment Phase by those not randomized to a structured maintenance programs) to their incremental QALY impacts. A bootstrap methodology will be used to estimate confidence intervals [101], and one-way sensitivity analyses will be performed to determine the robustness of our estimates to different assumptions such as to the wage rates used to value productivity [102]. Combined LBP and non-LBP-related healthcare utilization will be used for all of these analyses. Sensitivity analyses using LBP-related utilization only will also be performed. All cost effectiveness analyses will use the ITT principle.

For the Treatment Phase, the PT protocol calls for all PT participants to receive 15 total sessions in 12 weeks. Adherence to the PT protocol is defined as completing 11 or more sessions. However, it is conceivable that in a “real world” practice situation, many clinicians would discharge a patient after fewer sessions if, in the therapist’s clinical judgment, there had been substantial clinical improvement and the participant reached all desired exercise targets. To address this, we will conduct additional sensitivity analyses to explore whether the comparative cost effectiveness of PT vs. yoga would be substantially different if physical therapists stopped treating the patient if clinical improvement was reached prior to the end of the 12 weeks and 15 sessions. PT implementation costs for this sensitivity analysis would be limited to only those PT sessions provided up to and including a visit where improvement was reached. For the purpose of this sensitivity analysis, we will *a priori* define the time point for improvement for a PT participant to be when they meet both of the following criteria: a reduction of ≥6 points in the participant’s MODI score from baseline (six points is widely considered the minimal clinically significant improvement in the MODI [103]) and successfully able to complete all recommended exercises at the targeted number of repetitions as displayed in Table 5.

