### Specific aims

Evidence from multiple studies supports a moderate benefit in cLBP for yoga as well as exercise therapy individually delivered by a physical therapist [35,43,59]. Education, in the form of physician advice and handouts, are a common part of primary care provided to patients with cLBP [15]. However, no studies to date have done a head-to-head comparison of the effectiveness of yoga, PT, and education for cLBP. To ultimately reduce disparities in cLBP for minority populations, patients, providers, and health insurers need to know how evidence-based complementary therapies, such as yoga, compare in effectiveness to more well-established treatments such as PT and education. If yoga is superior to education and has similar effectiveness as PT, but costs less and has greater adherence, the potential therapeutic and economic implications would be substantial. Alternatively, if yoga is inferior, this information will help guide better treatment decisions and reduce unnecessary expenditures on inferior treatments.

The present study (“Back to Health”) is a 52-week randomized controlled trial of once-weekly yoga classes, individually-delivered PT, and education for cLBP in 320 individuals from predominantly low-income minority backgrounds recruited from BMC and affiliated community health centers. The trial starts with an initial 12-week Treatment Phase followed by a 40-week Maintenance Phase. Back to Health has the following three specific aims:

1. In the 12-week Treatment Phase, compare the effectiveness between a structured protocol of one yoga class per week, an individually-delivered structured PT protocol established around evidence-based clinical guidelines, and an educational book on self-care for cLBP.

2. In the 40-week Maintenance Phase, compare the effectiveness between patients participating in a structured yoga maintenance program, a structured PT maintenance program, or no structured maintenance program.

3. Determine the cost-effectiveness of yoga, PT, and education for adults with cLBP at 12 weeks, 6 months, and one year from three perspectives: society, third-party payer, and the participant.

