#### Cost effectiveness

We use a multi-method approach to collect cost data at 6, 12, 26, 40, and 52 weeks. Since our interventions may influence other common comorbidities of cLBP (e.g., depression [88] and obesity [89]), we measure total medical utilization, not only back-related utilization. Direct medical costs are measured, which consist of the cost of i) implementing the interventions themselves and ii) ongoing medical utilization during and after the intervention. Intervention implementation costs (e.g., non-study-specific staff hours, materials, facility use) are captured from study records and valued at their actual costs. Ongoing medical utilization including visits, hospitalizations, tests, radiology, and medications are taken directly from claims data, the BUMC Clinical Data Warehouse integrated databases, and electronic medical record systems. Direct medical costs are valued at their actual costs to the community health centers and BMC. Any non-insurance reimbursed medical utilization (e.g., acupuncturists, chiropractors, out-of-pocket back-related expenses) are obtained from a cost questionnaire adapted from previous studies [90] and are valued at the reported actual price paid by participants. The validity of the cost questionnaire is supported by a take-home cost diary [91]. The diary acts as a prompt for participants between data collection points to note visits to health practitioners, other health-related expenses, and non-medical direct costs (e.g., travel to yoga classes, childcare). This combination approach takes advantage of the fact that a diary can better capture a broad range of day-to-day costs, but a questionnaire can capture costs in a more consistent format with lower patient burden [92-94]. Direct non-medical costs for this study mainly consist of participants’ actual travel costs to the yoga and PT interventions, any childcare costs during those sessions, and the cost of any sessions attended after the Treatment Phase for patients not randomized to receive structured maintenance yoga or PT. These non-medical costs are valued at the reported actual price paid by participants. Unpaid childcare is valued at an average wage rate [95]. Indirect costs (i.e., lost productivity) for employed participants are calculated as the number of lost productive hours multiplied by a national average cost of employment for each participant’s general job category [96]. Lost productivity costs for those not in the workforce is assumed to be captured by their report of overall quality of life [97]. Lost productivity costs for those looking for work will be considered in sensitivity analyses. QALYs will be calculated based on the Short Form-based 6-Dimensional Measure of Health-Related Quality of Life, which is estimated from the results of the SF-36 using a previously developed algorithm [98,99].

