### Compensation to participants

Participants receive honoraria for participating in the study in the form of store gift cards (e.g., Target, CVS). We give the cards to participants after they complete each survey, according to the following schedule: baseline $50, 6 weeks $50, 12 weeks $100, 26 weeks $50, 40 weeks $50, 52 weeks $100. Each participant interviewed for the qualitative analyses also receives a gift card worth $25. We also encourage participants to update their contact information regularly throughout the study if it changes by giving $5 gift cards for providing verifiable updated contact information (e.g., new cell phone number). Participants receive study interventions (yoga classes, PT sessions, educational materials) and materials (e.g., yoga supplies, PT home practice materials, education book) free of charge.

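### In the participant-perspective cost analysis, study sessions enter at a fee of zero while outside sessions enter at the price paid, so these comparisons partly reflect the trial's subsidy

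*Protocol article*

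**What the plan says.** Aim 3 (Specific aims) is to determine the cost-effectiveness of yoga, PT and education "at 12 weeks, 6 months, and one year from three perspectives: society, third-party payer, and the participant". Under Study Design the article hypothesizes that yoga will be more cost-effective than PT.

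**Participant perspective.** Cost effectiveness analyses compares participants' incremental out-of-pocket costs with their incremental QALYs. The items are "travel, childcare, over-the-counter medications, use of non-reimbursed healthcare practitioners, co-payments" and the "cost of yoga or PT sessions attended after the 12-week Treatment Phase by those not randomized to a structured maintenance programs". The data-collection section on cost effectiveness lists travel, childcare and the same post-treatment sessions as direct non-medical costs and adds: "These non-medical costs are valued at the reported actual price paid by participants".

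**What participants pay for study treatment.** Compensation to participants states: "Participants receive study interventions (yoga classes, PT sessions, educational materials) and materials (e.g., yoga supplies, PT home practice materials, education book) free of charge".

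**Payer and societal perspectives.** The payer analysis uses "direct medical costs (direct intervention costs plus ongoing direct medical utilization costs"). Implementation costs "are captured from study records and valued at their actual costs", and the article also says: "Direct medical costs are valued at their actual costs to the community health centers and BMC". The societal analysis is the designated reference case. It takes direct medical and non-medical costs plus productivity.

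**Sensitivity analyses named.** These are wage rates (as an example of one-way analyses), utilization related to low back pain only, lost productivity of those looking for work, and a scenario in which PT costs stop once a participant has improved.

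**The concern.** A participant-perspective result is useful to a patient deciding whether to take up, or continue with, yoga or PT. Outside the trial that patient would meet a class fee or a co-payment. Inside the trial the study pays, and the costing rule records the in-trial price.

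Two comparisons are exposed:

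- **Maintenance versus no maintenance.** The yoga maintenance group is offered a free weekly class for 40 weeks. The yoga no-maintenance group is given a list of community classes and encouraged to attend them (Yoga maintenance). One group's sessions cost nothing by design. The other group's sessions are charged at what was paid.
- **Yoga versus PT.** Both enter with no session fee, so their participant costs can differ only through travel, childcare and other care. Yet the article describes PT as an insured benefit (Physical therapy maintenance) and treats reimbursement of yoga as an open question (Cost effectiveness analyses). The two are unlikely to cost a patient the same outside the trial.

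**Working it through.** The article states no cost figure to reproduce. The rules can be set side by side and their consequence worked out in symbols, then illustrated with assumed prices.

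**Inputs from the article.** Yoga: 12 Treatment Phase classes and up to 40 maintenance classes, 52 in all. PT: 15 + 5 = 20 sessions. Fee to participants for study sessions: $0.

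**Assumptions, not in the documents.** A charge per session of $5 to $40. Attendance and outside uptake as stated below.

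**1. Maintenance versus no maintenance, session fees only.** Let f be the fee per session, a the study maintenance sessions attended, and m the outside sessions bought by a no-maintenance participant.

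- As planned: 0 − f·m = −f·m, which is zero or negative whatever f and m are.
- With study sessions priced: f·a − f·m = f·(a − m).
- Gap between the two: f·a, which does not depend on m.

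Size of the gap at full attendance:

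| Assumed charge | Yoga, a = 40 | PT, a = 5 |
|---|---|---|
| $5 | $200 | $25 |
| $10 | $400 | $50 |
| $20 | $800 | $100 |
| $40 | $1,600 | $200 |

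Example for yoga with f = $10, a = 30 and m = 5: as planned, −10 × 5 = −$50; priced, 10 × (30 − 5) = +$250. The sign of the fee component changes.

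**2. What travel and childcare do to that sign.** These are counted for study sessions. Let t be travel plus childcare per study class, and suppose it is counted for study classes only. In the same example the planned difference is −50 + 30t, which is zero at t = 50/30 = $1.67. Above that, maintenance already comes out dearer for the participant under the plan. The fee component has a fixed direction; the total does not.

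**3. Yoga versus PT at 12 weeks, session fees only.** With class fee f and co-payment c, at full attendance:

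- As planned: 0 − 0 = 0.
- Priced: 12f − 15c. Over $5 to $40 for each, yoga is 12 × 5 = $60 to 12 × 40 = $480, and PT is 15 × 5 = $75 to 15 × 40 = $600.
- The difference runs from 60 − 600 = −$540 to 480 − 75 = +$405, and is zero when f = 15c/12 = 1.25c.

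The omitted component can favour either treatment, depending on prices the article does not give.

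**4. Do the named sensitivity analyses cover this?** No. Wage rates and lost productivity do not touch session fees. Restricting utilization to low back pain leaves study sessions at zero. The early-improvement scenario changes how many PT sessions are costed as implementation cost, which is not an item in the participant perspective.

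**The case against.** The strongest defence is that out-of-pocket spending in the trial is a coherent and openly stated definition. It agrees with the statement that study treatment is free, and no two passages contradict each other. This stands, and it is why the in-trial result should be kept.

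The alternative also has a weakness. It applies market fees to attendance and QALYs observed when sessions were free, and participants who had to pay might have attended less. This stands too. The priced result is a scenario, not an observed state of affairs.

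It may be said that the one-way sensitivity analyses are open-ended and that price scenarios can be left to a fuller plan. That carries some weight for the unit prices themselves. It carries less for the costing rule, which the article fixes explicitly and asymmetrically.

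A reader might go further and infer that the payer analysis is also mispriced, because it uses provider or study cost although its purpose is to inform reimbursement of yoga. The documents do not support a size or a direction for such an error. They give no reimbursement rates. PT is delivered partly by a private clinic network (Study sites), so its actual cost may already be a contracted price. Delivery cost is itself relevant to a reimbursement decision. Moving PT alone to a reimbursement rate, with no matching basis for yoga, would put the two arms on different price bases.

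**Conclusion.** The point holds for the participant perspective only. Its maintenance versus no-maintenance and yoga versus PT comparisons partly reflect who paid for the sessions in the trial, and no named sensitivity analysis shows by how much. The omitted fee per participant is the assumed charge times the sessions attended. Every dollar figure here rests on assumed charges and on the stated attendance.

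Two stronger readings should be resisted. One is that Aim 3 as a whole is mispriced: the societal reference case includes intervention costs at actual cost and is not affected, and the payer analysis includes them as well. The other is that structured maintenance is bound to look cheaper: that is true of session fees alone, but travel and childcare still count and the net direction is unknown. No incremental ratio is given here because the article states no expected QALY difference.

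This is a modest and inexpensive improvement to one of three perspectives, not an error that invalidates the economic analysis.

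**What to change.** In Cost effectiveness analyses, prespecify a second participant-perspective analysis beside the in-trial out-of-pocket result:

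- Charge each attended study session, and the supplies provided, at the price a patient would face outside the trial: a community class fee for yoga and a co-payment for PT.
- Apply this to Treatment Phase and structured maintenance sessions alike, and keep outside sessions at the price paid.
- State the unit prices, their source and the range over which they are varied.
- Report both results together, and note that attendance was observed when sessions were free.

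For the payer perspective, at most add one sensitivity analysis that values yoga and PT on a common payer-price basis. Do not move one arm alone.

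The cost is analysis work. Session attendance is already needed for the adherence definitions, so no new participant data are required. The unit prices must be assumed and justified. The article reports that recruitment is still under way, so the change can be fixed before the analysis.

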#### Physical therapy

We used evidence-based evaluation and treatment methods for the PT intervention [39,66-68]. Evidence indicates classifying patients based on clinical characteristics and tailoring the management strategy will improve the effectiveness of the PT intervention. Information from the history and examination is used to place cLBP patients into one of two subgroups based on the pattern of signs and symptoms. Treatment is then based upon the participant’s subgroup classification (Figure 2). Physical therapists receive approximately 12 hours of training prior to participating in the study. Training includes an online web-based modular curriculum, in-person training led by [name], [name], and other senior physical therapists experienced in the protocol, review of a PT training manual (Additional file 3), and practice on non-study patient volunteers. Each PT participant has an initial intake evaluation by a physical therapist and is classified into one of two mutually exclusive subgroups: Specific Exercise or Stabilization. Within the Specific Exercise group, there are “flexion” and “extension” subgroups. Specific Exercise flexion participants receive lumbar flexion exercises. Specific Exercise extension participants receive lumbar extension exercises. Stabilization participants receive exercises to strengthen core trunk muscles (Table 5) [69]. Participants’ classification is reassessed at each visit with appropriate adjustments to recommended exercises made. Since the evidence suggests that manipulation be used primarily for acute LBP episodes, manipulation is not part of our treatment protocol [39]. In addition, passive modalities such as heat, ice, ultrasound, and TENS are not employed. Weekly completion of the Modified Oswestry Disability Index (MODI; range of possible scores 0 to 50, with higher scores indicating greater disability) is used internally by PT staff to monitor participant progress.

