**Figure 2 F2:**
[figure not shown]
**Physical therapy intervention: the treatment-based classification algorithm.** Information from the history and examination is used to place chronic low back pain participants into one of two subgroups based on the pattern of signs and symptoms. Treatment is then based upon the participant’s subgroup classification. Participants’ classification is reassessed at each visit with appropriate adjustments to recommended exercises made. Participants are also classified according to the Fear Avoidance Belief Questionnaire (FABQ). PT participants who score ≥29 on the FABQ-W subscale receive *The Back Book* which provides brief cognitive behavioral education aimed at lowering fear avoidance. Physical therapists reinforce these points during treatment sessions and the participant’s exercise prescription is graded.

**Table 5 T5:** Physical therapy stabilization exercise protocol

**Primary muscle group**	**Exercises**	**Criteria for progression**
*Transversus abdominus*	Abdominal bracing	30 repetitions with 8 s hold
	Bracing with heel slides	20 repetitions per leg with 4 s hold
	Bracing with leg lifts	20 repetitions per leg with 4 s hold
	Bracing with bridging	30 repetitions with 8 s hold, then progress to 1 leg
	Bracing with standing	30 repetitions with 8 s hold
	Bracing with standing row exercise	20 repetitions with 6 s hold
	Bracing with walking	10 minutes with cycles of 8 s hold and 10s rest
*Erector spinae-multifidus*	Quadraped arm lifts with bracing	30 repetitions with 8 s hold on each side
	Quadraped leg lifts with bracing	30 repetitions with 8 s hold on each side
	Quadraped alternative arm & leg lifts w/ bracing	30 repetitions with 8 s hold on each side
*Quadratus lumborum*	Side support with knees flexed	30 repetitions with 8 s hold on each side
	Side support with knees extended	30 repetitions with 8 s hold on each side
*Oblique abdominals*	Side support with knees flexed	30 repetitions with 8 s hold on each side
	Side support with knees extended	30 repetitions with 8 s hold on each side

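### The early-discharge PT cost scenario scores improvement against a Stabilization-only table and shortens session costs while leaving QALYs unchanged

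*Protocol article*

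**What the plan says.** The protocol article, under Cost effectiveness analyses, notes that "the PT protocol calls for all PT participants to receive 15 total sessions in 12 weeks" and that "Adherence to the PT protocol is defined as completing 11 or more sessions". Because therapists in ordinary practice might discharge an improved patient sooner, it adds: "we will conduct additional sensitivity analyses to explore whether the comparative cost effectiveness of PT vs. yoga would be substantially different" under earlier stopping. In that scenario PT implementation costs are "limited to only those PT sessions provided up to and including a visit where improvement was reached".

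The improvement visit is defined in advance by two conditions that must both hold. One is a MODI reduction of at least 6 points from baseline. The other is that the participant is "successfully able to complete all recommended exercises at the targeted number of repetitions as displayed in Table 5".

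The caption of Table 5 reads "Physical therapy stabilization exercise protocol", and its rows are bracing, quadruped and side-support exercises. The Physical therapy section puts each participant in either Specific Exercise or Stabilization, never both at once, and ties only Stabilization to Table 5. In the other subgroup, "Specific Exercise flexion participants receive lumbar flexion exercises", and the extension subgroup likewise receives extension exercises.

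QALYs come from the SF-6D, derived from the trial's SF-36, and all cost-effectiveness analyses follow intention to treat. The scenario states no change to QALYs.

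**The concern.** Two separate problems sit in one rule.

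First, the exercise condition has no target for someone doing flexion or extension exercises. Two analysts could score the same participant in opposite ways. One would say the condition is never met, so all attended sessions are costed. The other would say it is met vacuously, so MODI alone decides. The rule is fixed a priori and names the table, so this is a defect in what is stated and not a detail left to another document.

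Second, the question posed is what happens if therapists stop treating earlier. Only the cost side is changed to match. The outcome data come from participants who were still offered the remaining sessions.

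Cost-effectiveness is the third specific aim, and the stated hypothesis is that yoga is more cost-effective than PT. This scenario checks whether a mandated 15-session course tilts that comparison against PT. If it cannot be scored consistently, and its benefit assumption is unstated, the check is hard to interpret.

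**Working it through.** The plan gives no cost or QALY result to reproduce. The nearest stated figure, PT adherence of 11 of 15 sessions, is 11/15 = 73.3% and agrees with the 73% in the adherence section.

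**1. Scoring rule against the table it cites.**
- The rule requires both conditions and names Table 5 for the second.
- Table 5 contains Stabilization exercises only.
- Specific Exercise participants receive lumbar flexion or extension exercises, which Table 5 does not list.
- Classification is reassessed at every visit, so someone who moves to Stabilization becomes scorable. Someone who stays in Specific Exercise does not.

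**2. Size of the scoring problem, by assumption.** The article gives no subgroup split, response rate or session of improvement. Let *s* be the share who remain in Specific Exercise, *p* the share of scorable participants who reach improvement, and *k* the session at which they do. Assume all 15 sessions are otherwise attended, and that *p* and *k* would be the same in both subgroups. Under the strict reading:

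share of full session cost counted = s + (1 − s) × [p × k/15 + (1 − p)]

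For p = 0.5 and k = 8 the bracket is 0.5 × 8/15 + 0.5 = 0.767. With s = 0.5 the share is 0.5 + 0.5 × 0.767 = 0.883.

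| k | p | all scorable | s = 25% | s = 50% | s = 75% |
|---|---|---|---|---|---|
| 6 | 0.7 | 58.0% | 68.5% | 79.0% | 89.5% |
| 8 | 0.5 | 76.7% | 82.5% | 88.3% | 94.2% |
| 11 | 0.3 | 92.0% | 94.0% | 96.0% | 98.0% |

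The saving found is (1 − s) times the saving that would be found if everyone could be scored. In the middle row it falls from 23.3% to 11.7% at s = 50%.

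**3. Size of the benefit assumption, by assumption.** Take the middle row with everyone scorable, and equal QALY gains across participants. Let early-discharged participants lose a fraction *f* of their gain. PT session cost per PT QALY, relative to the full course, is 0.767/(1 − p × f):
- f = 0: 0.767, which is what the scenario credits
- f = 0.1: 0.767/0.95 = 0.807
- f = 0.2: 0.767/0.90 = 0.852
- f = 0.3: 0.767/0.85 = 0.902

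These are average session-cost ratios within the PT arm. They are not incremental ratios against yoga, which also depend on utilization, productivity and the comparator.

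**4. Direction.** Step 2 makes PT look more expensive in the scenario than intended. Step 3 makes it look better value if stopping early costs any benefit. The two pull in opposite directions.

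**The case against.** The case against rests on five points.

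- **Subgroup membership is not permanent.** Reassessment at each visit means some who start in Specific Exercise may reach Table 5 exercises. The treatment algorithm figure and the PT manual are not shown and may hold flexion or extension targets. This stands in part: a reader might infer that Specific Exercise participants can never qualify, and that goes too far. It does not rescue those who stay in that subgroup, because the rule cites Table 5 and not the manual.
- **Neither cost nor benefit is that of a full 15-session course.** A reader might infer that 15 sessions are charged and the full 15-session benefit credited. The text counts sessions provided, and the analysis is by intention to treat, so both reflect actual attendance. This stands.
- **Changing cost while holding effect fixed is ordinary one-way sensitivity analysis.** It is legitimate as a bound. But the text presents it as an answer about stopping earlier and does not state the assumption of no lost benefit.
- **Loss of benefit is not shown.** Those discharged would already have improved, and home exercise is recommended. This is fair: the documents do not establish any loss. They do justify 15 sessions as a high dose that lets participants learn the regimen thoroughly, so retention of all benefit should not be assumed silently.
- **This is one additional, exploratory scenario.** This stands and limits the weight of the point.

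**Conclusion.** The point holds as a defect in one pre-specified sensitivity analysis. The exercise condition has no applicable target for participants who remain in Specific Exercise. Under the strict reading their attended sessions are all costed and the saving is understated in proportion to their share. Separately, shortening costs while keeping observed QALYs is a best case for PT on the benefit side, and it is not labelled as one.

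A reader might conclude that the scenario will give a wrong PT-versus-yoga answer. The documents do not support that. They give no subgroup split, improvement rate, timing, unit cost or QALY gain, and the two problems act in opposite directions, so neither net direction nor size can be derived. Every percentage above rests on assumed values of *s*, *p*, *k* and *f*. The reference case, the three cost perspectives and the co-primary outcomes are unaffected. The correction is worth making before analysis because it is cheap and removes an ambiguity that could otherwise be settled after seeing the data.

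**What to change.** For this analysis only, and without touching how therapists treat or discharge anyone:

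1. Replace the Table 5 reference with a scoring rule for each PT classification. Stabilization keeps Table 5. For Specific Exercise, use the MODI criterion plus completion of the participant's own prescribed exercises as recorded on the PT flow sheets, and say how a participant who changes classification is scored.
2. Label the cost-only version as assuming that no benefit is lost by stopping early.
3. Add a scenario that varies the share of QALY gain retained by early-discharged participants over a stated range, for example 70% to 100%.

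A tempting alternative to item 3 is to freeze SF-6D at the last value on or before the improvement visit. It works badly here: the SF-36 is collected only at baseline, 6 and 12 weeks in this phase, so anyone improving before week 6 would be given no gain at all.

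The flow sheets and SF-36 data are already collected. The cost is a few sentences, one extra scenario, and a less favourable figure for PT in that scenario.
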